## **4. STATISTICAL PROCEDURES**

### **4.1 SAMPLE SIZE CALCULATION**

A total of 35 patients will be recruited to the trial and treated by the application of the 2-OCA surgical sealant to the surface of the pancreatic remnant after DP. This sample size is judged sufficient for the evaluation of safety and applicability in this setting. If the trial proves safety of the intervention, a multicenter efficacy RCT will be conducted consecutively.

### **4.2 ANALYSIS VARIABLES AND STATISTICAL METHODS**

All patients treated with the trial intervention will be considered in the final analysis.

The empirical distribution of all endpoints will be calculated, including mean, standard deviation and quartiles in case of continuous variables and scores, and with absolute and relative frequencies in case of categorical data. 95% confidence intervals will be calculated. Whenever appropriate, statistical graphics will be used to visualize the findings.

Missing data will be minimized by consequent documentation and all other reasonable methods. No interpolation of missing data will be performed.

(Serious) adverse events will be summarized using descriptive statistics. The adverse events will be categorized as surgical, cardiovascular, pulmonary, urinary and other complications. Furthermore, it will be defined if events were device-related or not. Device-related and not device-related (serious) adverse events will be reported separately. Proportions and frequencies of adverse events will be presented. Specific focus will be placed on potential device-related adverse events.

Because the BOND-Trial is designed as a proof-of-concept trial no formal analyses will be conducted. In case of safety and feasibility, the results will serve as a basis for sample size calculation (set into relation to the results from previous RCTs) for a succeeding randomized controlled trial.

## **5. QUALITY ASSURANCE**

### **5.1 CLINICAL DATA MONITORING**

During the clinical trial, quality control and quality assurance will be ensured via monitoring, auditing and inspections by the competent authorities, if and when applicable. All investigators agree that the monitor can visit the center before, during and after completion of the study to ensure that the study is conducted, recorded and reported according to the study protocol, relevant standard operating procedures, requirements of GCP and the applicable regulatory requirements (e.g. DIN EN ISO 14155). In addition, audits can be conducted by the sponsor and/or by the competent authorities in accordance with ICH-GCP and DIN EN ISO 14155.[33] The aim of auditing is to assure that all results and conclusions written in the

|      |                      |            |
|------|----------------------|------------|
| BOND | Protocol version 3.2 | 12.11.2014 |
|------|----------------------|------------|

final report can be drawn from the source data. This includes controlling of data filing and organisation of the study center as well as controlling of third parties and original documents.

## 5.2 ASSESSMENT OF SAFETY

### Definition and Documentation of Adverse Events

According to ISO 14155 an adverse event is any untoward medical occurrence, unintended disease or injury, or untoward clinical sign (including abnormal laboratory findings) in subjects, users or other persons, whether or not related to the investigational medical device.

Note:

This definition includes events related to the investigational medical device or the comparator.

This definition includes events related to the procedures involved.

For users or other persons, this definition is restricted to events related to investigational medical devices.

An AE may be:

- new symptom/ medical condition,
- new diagnosis,
- changes of laboratory parameters,
- intercurrent diseases and accidents,
- worsening of medical conditions/ diseases existing before clinical trial start,
- recurrence of disease,
- increase of frequency or intensity of episodic diseases.

A pre-existing disease or symptom will not be considered an adverse event unless there will be an untoward change in its intensity, frequency or quality. This change will be documented by an investigator.

Surgical procedures themselves are not AEs; they are therapeutic measures for conditions that require surgery. The condition for which the surgery is required may be an AE. All AEs (including SAEs) will be documented on an AE-form. AEs are classified as "non-serious" or "serious".

#### Serious Adverse Event (SAE)

According to the Ordinance on Medical Devices Vigilance (Medizinprodukte-Sicherheitsplanverordnung, MPSV), a serious adverse event (SAE) is defined as follows:

Any untoward event in a clinical trial which is subject to approval that indirectly or directly led, might lead or might have led to death or a serious deterioration in state of health of a patient, user or other person and which does not necessarily have a causal relationship to the medical device, with one of the following outcomes:

|      |                      |            |
|------|----------------------|------------|
| BOND | Protocol version 3.2 | 12.11.2014 |
|------|----------------------|------------|

- a. death
- b. a serious deterioration in state of health of the patient which led to a
  - 1) life- threatening illness or
  - 2) permanent impairment of a body function or permanent damage to a body structure or
  - 3) requirement of subject hospitalization or prolongation of existing hospitalization,
  - 4) necessity of medical or surgical intervention to prevent permanent impairment of a body function or permanent damage to a body structure
- c. foetal distress, foetal death or any congenital abnormality or birth defects

Note:

Planned hospitalization for a pre-existing condition, or a procedure required by the protocol, without serious deterioration in health, is not considered a serious adverse event.

#### Adverse Device Effect (ADE)

An adverse device effect is an adverse event related to the use of an investigational medical device.

#### Serious Adverse Device Effect (SADE)

A serious adverse device effect is a device effect that has resulted in any of the consequences characteristic of a serious adverse event.

#### Unanticipated Serious Adverse Device Effect (USADE)

An unanticipated serious adverse device effect (USADE) is a serious adverse device effect which by its nature, incidence, severity or outcome has not been identified in the current version of the risk analysis report, as contained in the investigator's brochure ("Handbuch des klinischen Prüfers").

In contrast, an anticipated serious adverse device effect (ASADE) is an effect which by its nature, incidence, severity or outcome has been identified in the risk analysis report.

All adverse events occurring during the period between the application of the medical device and the last follow-up visit must be documented on an "Adverse Event Form" in the CRF. All untoward medical occurrences appearing prior to the application of the medical device will be recorded as medical history.

#### Classification of Intensity

The intensity of a SAE will be classified as follows:

- Mild:* Temporary event which is tolerated well by the subject
- Moderate:* Event which results in discomfort for the subject and impairs his/her normal activity
- Severe:* Event which results in substantial impairment of normal activities of subject

|      |                      |            |
|------|----------------------|------------|
| BOND | Protocol version 3.2 | 12.11.2014 |
|------|----------------------|------------|

### Classification of Outcome

The outcome of a SAE at the time of last contact with the subject is classified.

*Ongoing:* Signs and symptoms of the SAE still exist.

*Recovered completely:* All signs and symptoms of SAE have disappeared.

*Recovered with sequelae:* Acute signs and symptoms of SAE have disappeared, sequelae caused by the SAE still exist.

*Death:* The SAE has caused the death of the patient. If a subject has suffered from more than one SAE, only the outcome for the SAE directly responsible for death is classified as 'death', the other SAEs are classified according to their specific outcome.

*Unknown:* The outcome is not known or is implausible and there is no possibility to complete or verify the information.

### Classification of Causality

The causality will be classified in a binary order:

Reasonable possibility that the trial intervention caused the SAE? YES/NO

If causality is "not assessable" it will be classified as NO.

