| Intervention(s)                      | Experimental intervention: Intraoperative 2-OCA application on pancreatic remnant in distal pancreatic resection (DP)
Follow-up per patient: 3 months
Duration of intervention per patient: 5 min application of the surgical sealant
Duration of complete operation: ~ 120-240 min                                                                                                                                                                                                                                                                                                                                                                                                                                                                                                                                                                                                                                                                                                                                                                                                                                                                                                                                                                                         |

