### Endpoints:

Primary safety endpoint:

- Frequency of serious adverse events and device-related adverse events (as categorized below)

Primary efficacy endpoint:

- Occurrence of a postoperative pancreatic fistula (according to the ISGPF definition [1]) within 30 days after the index operation.

Secondary endpoints:

- Surgical:
  - Delayed gastric emptying (according to the ISGPS definition) [2]
  - Postpancreatectomy hemorrhage (according to the ISGPS definition) [3]
  - Postoperative pancreatitis
  - Intra-abdominal abscess or fluid collection
  - Relaparotomy
  - Burst abdomen
  - Wound infection
- Cardiovascular:
  - Perioperative myocardial infarction
  - Perioperative cerebral vascular incident
  - Perioperative deep vein thrombosis
- Pulmonary:
  - Perioperative lung embolism
- 30-day mortality
- Operation time
- Intraoperative blood loss
- Postoperative hospital stay

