### Reporting of Serious Adverse Events

#### *Immediate Reporting*

According to § 3 (5) of the Ordinance on Medical Devices Vigilance (Medizinprodukte-Sicherheitsplanverordnung, MPSV), last updated on July 25th, 2014, all SAEs have to be reported immediately by the investigator to the sponsor.

The sponsor will report immediately to the national competent authority (Bundesinstitut für Arzneimittel und Medizinprodukte - BfArM) all SAEs concerning subjects, users or others, for which a causal relationship with the medical device under investigation, with applied diagnostic or therapeutic measures or other conditions of the clinical trial cannot be excluded. All reports will be sent electronically using the latest version of the report form provided on the BfArM website

|      |                      |            |
|------|----------------------|------------|
| BOND | Protocol version 3.2 | 12.11.2014 |
|------|----------------------|------------|

([http://www.bfarm.de/SharedDocs/Formulare/DE/Medizinprodukte/Meldeformular\\_Klinische-Pruef\\_SAE.pdf?\\_\\_blob=publicationFile&v=4](http://www.bfarm.de/SharedDocs/Formulare/DE/Medizinprodukte/Meldeformular_Klinische-Pruef_SAE.pdf?__blob=publicationFile&v=4)).

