### *Periodic Reporting*

All SAEs which do not fulfill the criteria for immediate reporting will be documented completely by the sponsor and summarized. They will be reported quarterly to the BfArM or upon request using the SAE reporting table form provided on the EC website ([http://ec.europa.eu/health/medical-devices/documents/guidelines/index\\_en.htm](http://ec.europa.eu/health/medical-devices/documents/guidelines/index_en.htm)).

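### Coding an SAE of not-assessable causality as unrelated can only lower the device-related part of the primary safety endpoint, and the rule is not reconciled with the immediate-reporting criterion

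*Protocol*

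**What the plan says.** Section 5.2, Classification of Causality, uses a two-level item: "Reasonable possibility that the trial intervention caused the SAE? YES/NO". It then adds: "If causality is 'not assessable' it will be classified as NO". The synopsis describes the intervention as "Intraoperative 2-OCA application on pancreatic remnant in distal pancreatic resection (DP", so the item in effect asks about the device.

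Section 2.3 defines the primary safety endpoint as "Frequency of serious adverse events and device-related adverse events (as categorized below". Section 4.2 says "Device-related and not device-related (serious) adverse events will be reported separately" and "Specific focus will be placed on potential device-related adverse events".

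Under Immediate Reporting in Section 5.2, the sponsor must report an SAE at once to the competent authority when causation remains open. The criterion is that a "relationship with the medical device under investigation, with applied diagnostic or therapeutic measures or other conditions of the clinical trial cannot be excluded". Periodic Reporting covers the rest: "All SAEs which do not fulfill the criteria for immediate reporting will be documented completely by the sponsor and summarized". Those go to the authority quarterly or on request.

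**The concern.** An event whose causality cannot be assessed carries no information that the device was not involved. Coding it as unrelated turns missing information into a favourable answer. It also leaves the adverse-device-effect classes in Section 5.2, because each of them requires a relationship to the device.

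This is a single-arm trial with unblinded assessors, so attribution rests on judgement. Visits 6 and 7 are telephone interviews, so late events may be poorly documented. Safety is the main objective, and a finding of safety opens the way to a multicenter RCT. The background evidence in Section 2.2.3 uses a more inclusive standard: it counts complications possibly related to 2-OCA in non-vascular use, 3 of 119 (2.5%). A trial rate that leaves out unassessable events would look better against that figure partly for reasons of definition.

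The same event also has an unclear place in the reporting rules. A relationship that cannot be assessed has not been excluded, which meets the immediate-reporting criterion, yet the event carries a code meaning no reasonable possibility of causation.

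**Working it through.** The protocol ties no event rate, threshold or power figure to this rule, so there is no stated figure to reproduce. The check has two parts.

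**Setting the texts side by side**

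1. *Direction.* The default moves events from not assessable to NO and never to YES. The device-related count can therefore fall or stay the same, but cannot rise.
2. *Reach within the endpoint.* The endpoint in Section 2.3 has two components: all SAEs whatever their cause, and device-related adverse events. A not-assessable SAE still counts in the first. It is lost only from the second, and it appears on the unrelated side of the Section 4.2 split.
3. *Reporting route.* The immediate route depends on whether a relationship with the device, with other measures applied or with trial conditions can be excluded. The quarterly route takes whatever does not meet that criterion. Neither text names the causality code as the trigger, and neither says that the code is irrelevant. The sponsor's review (Actions of Sponsor) re-determines the relationship to the device but has no rule for the not-assessable case. The authority's form in Appendix III offers both yes and possible for each relation; the protocol's item has no level matching possible.
4. *Scope.* The causality item is worded for SAEs. The endpoint counts device-related adverse events of any seriousness, and Section 4.2 requires adverse events in general to be designated device-related or not. For non-serious events Section 5.2 gives no matching causality item.

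**Size**

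Inputs:
- n = 35 patients (Sections 2.1.1 and 4.1); n = 30 as a variant, because the synopsis gives 30 to be analyzed.
- Two-sided 95% confidence intervals (Section 4.2). The method is not named; exact Clopper-Pearson intervals are assumed.
- k = number of patients whose only possibly device-related event is a not-assessable SAE. The protocol does not give k, so a range is assumed. It is also assumed that no event is clearly related.

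Formulas: rate = k/n; lower limit = Beta(0.025; k, n − k + 1), or 0 if k = 0; upper limit = Beta(0.975; k + 1, n − k). Here Beta(p; a, b) is the p-quantile of the beta distribution.

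As written, the count is 0 for every k. With n = 35 the upper limit is 1 − 0.025^(1/35) = 10.0%, so the report reads 0/35 = 0% (0 to 10.0%).

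If not-assessable events are counted as related, n = 35:
- k = 1: 1/35 = 2.9% (0.1 to 14.9)
- k = 2: 2/35 = 5.7% (0.7 to 19.2)
- k = 3: 3/35 = 8.6% (1.8 to 23.1)
- k = 5: 5/35 = 14.3% (4.8 to 30.3)

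With n = 30, the rule gives 0/30 = 0% (0 to 11.6), against 3/30 = 10.0% (2.1 to 26.5) for k = 3.

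Each affected patient therefore takes 1/35 = 2.9 percentage points off the reported device-related rate.

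**The case against.** The strongest reply is that the texts govern different things. The causality item classifies events; the immediate-reporting criterion directs the sponsor, is wider than the device, and is the only criterion that the quarterly rule refers to. An SAE can be coded NO and still be reported at once. All SAEs go to the sponsor immediately, the sponsor determines the relationship in writing, the authority is informed of all SAEs, and the DSMB receives a safety report at least every three months. This stands. A reader might infer that the two rules cannot both be followed, or that immediate reports will be delayed, but the documents do not show that. What remains is that a NO code could be read as pointing to the quarterly list, and nothing says it does not.

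A second reply is that a reasonable possibility is a low bar. A collection beside the sealant with a plausible link would be YES, so not assessable is a residual class and may be small. This also stands, and it is why the size is shown only as a range. A reader might use the roughly 10 fistulas in Section 2.1.1 to argue that several such events are likely. That figure is the number expected without the sealant, and the protocol does not say that those fistulas would be serious or unassessable.

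A third reply is that the analysis is descriptive, with no test or threshold on the device-related rate, and both sides of the split are reported. That limits the harm, but the device-related rate and its interval are still a primary result.

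**Conclusion.** The point holds for the device-related component of the primary safety endpoint and for the related/unrelated split in Section 4.2. The protocol states a fixed rule here, so this is not a detail left open for an analysis plan. The rule works in one direction only. If no event is clearly related and one to three of 35 patients are affected, the report shows 0% with an upper limit of 10.0%, where the conservative count shows 2.9% to 8.6% with upper limits of 14.9% to 23.1%. If no SAE is unassessable, nothing changes.

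Two stronger readings are not supported. A reader might infer that the primary safety endpoint as a whole is biased, but its all-SAE component counts these events regardless. A reader might also stress that this is the first use of the substance in this organ, but Sections 1.1 and 2.2.3 describe earlier topical 2-OCA use at the pancreaticojejunal anastomosis, with 75 treated patients.

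The relation to the immediate-reporting rule is an unreconciled gap in the text, not a proven contradiction.

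**What to change.** Replace the default sentence under Classification of Causality so that:

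- not assessable is recorded as a category of its own;
- it is counted with the device-related events in the main device-related tabulation and shown there on a separate line;
- a sensitivity tabulation counts it as not related.

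Keep the reasonable-possibility question for events that can be assessed. Making every event whose relationship cannot be excluded a YES would go too far: in an uncontrolled surgical trial it could draw in most local postoperative SAEs and leave the split uninformative.

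State that the causality code does not decide the reporting route, and reconcile the item with the Immediate Reporting text by a cross-reference. Word the item for all adverse events, to match the endpoint.

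The cost is one replaced sentence with its cross-reference, one CRF box, and a device-related rate that may look slightly less favourable.

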### Classification of Countermeasures

The countermeasures will be documented according to the following rules:

*None:* No action taken

*Drug treatment:* Newly-prescribed medication or change in dose of a medication

*Others:* Other countermeasures, e.g. an operative procedure

### Reporting of Serious Adverse Events

#### *Immediate Reporting*

According to § 3 (5) of the Ordinance on Medical Devices Vigilance (Medizinprodukte-Sicherheitsplanverordnung, MPSV), last updated on July 25th, 2014, all SAEs have to be reported immediately by the investigator to the sponsor.

The sponsor will report immediately to the national competent authority (Bundesinstitut für Arzneimittel und Medizinprodukte - BfArM) all SAEs concerning subjects, users or others, for which a causal relationship with the medical device under investigation, with applied diagnostic or therapeutic measures or other conditions of the clinical trial cannot be excluded. All reports will be sent electronically using the latest version of the report form provided on the BfArM website

|      |                      |            |
|------|----------------------|------------|
| BOND | Protocol version 3.2 | 12.11.2014 |
|------|----------------------|------------|

([http://www.bfarm.de/SharedDocs/Formulare/DE/Medizinprodukte/Meldeformular\\_Klinische-Pruef\\_SAE.pdf?\\_\\_blob=publicationFile&v=4](http://www.bfarm.de/SharedDocs/Formulare/DE/Medizinprodukte/Meldeformular_Klinische-Pruef_SAE.pdf?__blob=publicationFile&v=4)).

### *Periodic Reporting*

All SAEs which do not fulfill the criteria for immediate reporting will be documented completely by the sponsor and summarized. They will be reported quarterly to the BfArM or upon request using the SAE reporting table form provided on the EC website ([http://ec.europa.eu/health/medical-devices/documents/guidelines/index\\_en.htm](http://ec.europa.eu/health/medical-devices/documents/guidelines/index_en.htm)).

### *Actions of Sponsor*

The sponsor has to assure, that every SAE will be reported by all investigators participating in this trial. Serious adverse events have to be reported by the attending physician to the principal investigator within 24 hours after the incident. The initial report must be as complete as possible including details of the current illness and (serious) adverse event and an assessment of the causal relationship between the event and the trial treatment.

The sponsor is responsible for the classification of serious adverse events and ongoing safety evaluation of the clinical investigation and shall review the investigator's assessment of all serious adverse events and determine and document in writing their seriousness and relationship to the investigational device; in case of disagreement between the sponsor and the investigator(s), the sponsor shall communicate both opinions.

The sponsor should assess whether corrective or preventive action is required. If the sponsor himself takes independently corrective actions to ensure the safety of subjects, users or others, the national competent authority and in this case also the ethics committee have to be informed immediately.

Reporting of serious adverse events to:

PD [name]  
Studienzentrum der Deutschen Gesellschaft für Chirurgie  
[name]  
[name]

|      |                      |            |
|------|----------------------|------------|
| BOND | Protocol version 3.2 | 12.11.2014 |
|------|----------------------|------------|

Pursuant to the German Medical Device Law (MPG) and the Ordinance on Medical Devices Vigilance (MPSV) the competent authority (BfArM) will be informed of all SAEs during the trial. The BfArM and the IEC (if necessary) will be informed in case the risk/benefit assessment changes or any other new and significant hazards for subjects' safety or welfare occur.

The competent authority must be informed within 90 days upon completion about the end of the trial. It will be provided with a summary of trial results within one year after the end of clinical phase (LPO) (see §23a MPG).

